## Abstract

**Background:**

Smoking is the leading behavioral risk factor for the loss of healthy life years. Many smokers want to quit, but have trouble doing so. Financial incentives in workplace settings have shown promising results in supporting smokers and their design influences their impact. Lotteries that leverage behavioral economic insights might improve the effectiveness of workplace cessation support.

**Methods and design:**

We examine in a cluster randomized trial if a workplace cessation group training paired with lottery deadlines will increase continuous abstinence rates over and above the cessation training alone. Organizations are randomized to either the control arm or lottery arm. The lotteries capitalize regret aversion by always informing winners at the deadline, but withholding prizes if they smoked. In the lottery-arm, winners are drawn out of all participants within a training group, regardless of their smoking status. In weeks 1-13 there are weekly lotteries. Winners are informed about their prize (€50), but can only claim it if they did not smoke that week, validated biochemically. After 26 weeks, there is a long-term lottery where the winners are informed about their prize (vacation voucher worth €400), but can only claim it if they were abstinent between weeks 13 and 26. The primary outcome is continuous abstinence 52 weeks after the quit date.

**Discussion:**

There is a quest for incentives to support smoking cessation that are considered fair, affordable and effective across different socioeconomic groups. Previous use of behavioral economics in the design of lotteries have shown promising results in changing health behavior. This cluster randomized trial aims to demonstrate if these lotteries are also effective for supporting smoking cessation. Therefore the study design and protocol are described in detail in this paper. Findings might contribute to the application and development of effective cessation support at the workplace.

**Trial registration:**

Netherlands Trial Register Identifier: NL8463. Date of registration: 17-03-2020.

**Supplementary Information:**

The online version contains supplementary material available at 10.1186/s12889-022-14915-x.

## Background

Tobacco use is causing 8.7 million deaths every year worldwide and remains the largest behavioral risk factor for noncommunicable disease and loss of healthy life years [1]. Moreover, approximately one third of socioeconomic inequalities in mortality are attributable to smoking [2]. Stopping smoking is, therefore, one of the most direct routes to increasing life expectancy up to 10 years and reducing socioeconomic inequalities in health [2, 3].

Next to the health burden, tobacco use also imposes substantial economic costs via health expenditures and through productivity losses [4]. Smoking is associated with reduced work performance and a 31% higher likelihood of workplace absenteeism; smokers annually take approximately three more sick days than non-smoking colleagues [5–7]. Estimates show that employers suffer an excess expense of $5816 annually to employ a smoker in comparison to a non-smoker [7].

Therefore, employers might benefit from facilitating smoking cessation support at the workplace. There is strong evidence that workplace cessation interventions such as group counseling, are effective in helping people to stop smoking [8]. In addition, especially among disadvantaged populations, accessibility, proximity and financial compensation are important aspects in the uptake of cessation interventions [9, 10], whereas broader and untargeted interventions may be less effective [9, 11]. Smoking cessation support at the workplace has the benefit of being a suitable nearby and familiar intervention-context, which can aid the necessary improvements in behavioral intervention design that are needed to realize more equal smoking cessation outcomes across socioeconomic positions [12].

Although the majority of smokers do not want to smoke and often try to quit, most attempts fail [13]. There are multiple factors that make quitting challenging. In addition to overcoming a physical addiction, quitting is difficult due to the time-gap between the immediate effort that is needed to quit and the mostly long-term benefits of quitting [14, 15]. In a ‘cold’ deliberative state smokers can genuinely set a long-term health goal, but when they are in a more ‘hot’ affective state, they may succumb to (overly present) immediate temptations. Tobacco is widely available and the nearby (social) benefits of smoking then outweigh the delayed benefits of quitting, resulting in lower levels of goal attainment [16, 17].

Financial incentives have the potential to help overcome this pattern because of their more immediate nature [18, 19]. Literature reviews show there is high-certainty evidence that incentives improve smoking cessation rates across mixed populations [20]. For example, a randomized trial with 61 businesses finds that an individual €350 incentive on top of a workplace cessation group training increased the proportion of abstinent employees 1 year later with 15 percentage points, compared to an only group training treatment [21]. Likewise, higher rates of smoking cessation up to 18 months are found when employees were offered a financial incentive ($750) on top of a smoking cessation program [22].

The configuration of incentives can influence their effect on behavior [23, 24]. Researchers crafting incentives for smoking cessation have to make decisions about the incentive’s form, timing, frequency, certainty and magnitude (see Adams et al., for a framework [23]). Literature reviews show no clear association between quit-rates and incentive size [20, 25]. While this largely shows a gap in research, it might also indicate that other important design features influence the effect of incentives on behavior [26].

A promising design used by behavioral economists and medical professionals is the use of *regret lotteries*, which have been demonstrated to support weight loss [27], medication adherence [28] and physical activity [29, 30] at relatively low costs [31] across differing populations [32]. By their design, the lotteries aim to tap into multiple psychological insights on decision-making, with the goal to gain as much health out of every euro spent. Most prominently, all participants can win the prize at the deadline and the winner is always informed about the outcome. However, winners can only keep their prize if they attained their own prespecified health goal. The promise of this counterfactual feedback is meant to leverage anticipated regret [33]. Although these lotteries have been effective in supporting multiple health behaviors with an intertemporal character, to the best of our knowledge, this particular design remains untested for smoking cessation.

### Aim and hypothesis

The aim of this paper is to describe the protocol for a cluster randomized trial “The Smoke-Free Lottery” which aims to investigate whether lotteries will increase the effectiveness of tobacco-cessation group training at the workplace. It is hypothesized that the lotteries increase continuous abstinence rates over and above cessation training alone.

## Methods/design

### Setting

This trial takes place in the Netherlands. Currently, 15 % of the adult Dutch population smokes daily (~ 2.1 million), which is lower than the average in the European Union. The percentage of daily smokers in the lowest income group is about twice as high as that in the highest income group. Likewise, lower educated adults include a double to triple percentage of smokers in comparison to the higher educated [34].

Approximately 31% of smokers took a serious attempt to quit in 2021, which is significantly lower than in 2020 (36%) [34]. Health insurance is mandatory and fully covers a registered cessation training (maximum of 1 per year). Medication during cessation training is covered by most insurers and the training itself is exempt from deductibles.

### Study design

We propose a two-arm, parallel group, cluster-randomized trial running for 52 weeks in 16 organizations (clusters) across the Netherlands. We aim to assign organizations to receive either a smoking-cessation training (8 companies) or a smoking-cessation training plus the smoke-free lottery (8 companies). Participants in both arms participate in an identical 8-week smoking cessation group training at the workplace. Participants in the lottery condition will additionally participate in 13 weekly lotteries starting from the prespecified joint quit date, complemented with a long-term lottery after 26 weeks. A schematic representation of the trial is presented in Fig. 1. The trial protocol and materials were reviewed and approved by the Radboud University Ethical Review Board (ECSW-2019-114). The study is registered in the Dutch Trial Register (NTR NL8463) and lottery drawings are performed by an independent notary.

**Fig. 1 Fig1:**
[figure not shown]
Trial flow and event schedule

## Participants

### Recruitment

For this trial we cooperate with SineFuma, a Dutch company that delivers smoking cessation training at the workplace. By email, flyers, newsletters, network contacts and social media, we will recruit organizations over the course of 1.5 years to facilitate a group cessation training and participate in the study. SineFuma also informs their new clients about the possibility to join the present study.

The recruitment of companies follows several steps, designed minimize recruitment bias at the company level and maximize clarity and ease for the companies. As a first step, companies are informed about the study and the fact that they will be randomized if they participate. A study staff member checks with the company if they meet all eligibility criteria, verbally or written. If a company agrees with randomization and meets the criteria, the third step is that the company sets up the planning for the group training with SineFuma and signs their written offer. Hereby the company commits to organizing and financing the training, but they do not know their allocation yet. For the next step, only after SineFuma communicates to the study staff that the interested company has financially and logistically committed to organizing the group-training, do we start the randomization procedure. This makes that companies can decline to participate in our trial because they dislike the idea of randomization, but minimizes the risk of recruitment bias by companies cancelling the entire program because they disagree with their allocation.

For the recruitment of employees, SineFuma typically organizes an information meeting for their cessation training at the workplace. The training and meeting are advertised internally by the companies via email, intranet, flyers and posters. At the information meeting, the study staff additionally informs the smokers about the study, using our folder, video and slides and explains how employees can enroll. Employees are informed that they can also join the group training without enrolling to the study.

Employees interested in the study can submit their email address. An information letter and screening questionnaire are sent by the study staff. Candidates can choose to participate in the study until the start of the first session of the smoking cessation program. This will be at least 1 week, up to several weeks, depending on the planning of the training.

Because we start recruitment of employees after allocation of the cluster, the lotteries might attract a proportion of participants that otherwise would not have joined the 8-week long cessation program. As such, the control group might to some degree exist of higher cessation-committed participants, reducing a potential treatment effect. To prevent this recruitment bias as much as possible, we designed three securities in our recruitment. First, we use highly similar standardized recruitment materials informing about a) the value and meaning of participation in a scientific study and b) the advantages and disadvantages of the required measurements and surveys. Second, participants are informed about the treatment that is relevant to them and that evaluating this treatment is the goal of our study. This means that we do not tell participants that they were randomized, therefore missed out on receiving incentives and are next being compared to the other treatment. Third, recruitment within the companies is focused largely on the cessation training through communication materials by SineFuma, as this is the core of the commitment. Candidates are informed about the study generally after information about the 8-week training.

### Eligibility criteria

For organizations to participate, the management should be willing to pay for the training and, if assigned to the lottery arm, to pay for the lotteries. They have to agree to participate prior to randomization. The management allows their employees to participate in the group training sessions and carbon monoxide (CO)-measurements during or shortly before or after working hours on a location hosted by the employer. After the outbreak of Sars-Cov-2, the training is hosted mostly online (see below), which dismisses the location-criterion.

For employees to participate, they need to have smoked tobacco (no e-cigarettes) for at least one pack-year (= number of daily packs x years), smoke daily, are willing to quit, want to join the group training and are at least 18 years old. Employees that are not able to read or speak Dutch are excluded from participation in this study, because the cessation training is in Dutch.

After expressing interest in the study, participants receive an information letter, a screening questionnaire and a written informed consent form. Ineligible candidates receive an e-mail and can participate in the cessation training, but not in the study and thus the lotteries.

### Randomization

Organizations (clusters) are randomized using a computer-generated biased urn schedule prior to the recruitment of individual participants. The biased urn method entails that the allocation probability changes based on the current balance [35]. As such, the probability of allocation to either arm depends on the level of organizations already randomized to that arm. Larger organizations with distinct subsidiaries or autonomous sub-departments can be randomized separately, only if treatment contamination can be avoided.

Allocation concealment at the organization level is ensured by first including the organization and randomizing after. Only after an explicit commitment by the organization, randomization is requested by the recruiting staff member to the randomizing staff member, in order to conceal knowledge of the upcoming assignment by the recruiters. We decided not to randomize at the participant level to avoid disappointment and possible attrition and to ease and unify recruitment of employees by employers.

### Blinding

Participants are not informed about the treatment in the other arm. Nonetheless, blinding cannot be fully guaranteed as a result of how organizations are publicly recruited. We do not inform participants that their treatment will be compared to another treatment. Researchers and the management of the companies could not be blinded due to the nature and multi-party coordination of the trial.

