### Retention

As a compensation for their participation in the study, participants are promised and given €30 at the end of the study, regardless of smoking status. To further prevent attrition and increase commitment to the study, we will hand all participants gadgets with the institute’s logo throughout the study (a water flask and mug) and send them a birthday and Christmas card on behalf of the study staff. Participants who do not respond to surveys or other measurements, receive a reminder text message and email.

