## Intervention

This trial compares a control-arm to an intervention-arm. All participants get an anonymized trial-ID at the start of the trial.

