### Smoking abstinence carbon monoxide measurement

To biochemically verify smoking status, we use the validated non-invasive iCOquit Smokerlyzer® (Bedfont Scientific Ltd). The iCO measures CO-levels by requiring smokers to breath into the device. It is a strictly personal device that all participants receive by mail to their home address. Participants are asked to connect the device to their smartphone in order to use accompanied app. A tailored manual and instruction video was made for this trial and is sent to participants. Previous studies using smartphone CO-meters have shown personal mobile meters are suited to distinguish smokers from non-smokers and that usability is high [50, 51].

Participants receive a text message, asking them to perform and share the CO-measurement. After the measurement, results are presented in the app, that also allows participants to directly share their results with the trial staff via mail. Following the RS, we use a cut-off point of ≤9 ppm (p.p.m.) to determine smoking status. Measurements are weekly from the start of the training until 13 weeks after the quit date (of which 7 measurements are in the weeks of the training), and once at 26 and 52 weeks. Between weeks 14-26 there is one unannounced measurement. Participants know that it will ensue, but not in which week. If there is a difference between self-reported abstinence and biochemical validation or when participants do not respond, participants are assumed to have smoked. Following the RS, a failed biochemical test classifies a participant as smoking even when this is explained by the recent smoking of one to five cigarettes allowed throughout the follow-up period [49].

To summarize, when a participant reports not to have smoked more than five cigarettes between the quit-day and week 52, and this can be biochemically verified at week 52, they are considered not to have smoked. If previous measurements contradict this according to the criteria above, the participant is not considered continuously abstinent.

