Another limitation of first randomizing employers and next starting the recruitment of employees, is that the training + lotteries arm might especially attract smokers who are interested in the lotteries (see *Recruitment).* However, allocating participants after enrollment does not fully rule out this motivation, as participants might still participate hoping to be randomized to the lottery arm, possibly enhancing disappointment after. The benefit of our approach is that we minimize demotivation and maximize clarity at the employee level early on. For example, several employers stated that they would only participate if they would be enrolled to the lottery arm, therefore did not meet our eligibility criteria and could not participate in the study. In the surveys, we attempt to assess motivation to participate among employees.

We require organizations to pay for the training and lotteries and require participants to own a smartphone. Therefore, a third limitation is that our recruitment strategy might favor relatively wealthier organizations and employees. This risk is minimized by the fact that the training is covered by employees’ health insurance (see *Setting)* and that the total lottery expenses are kept low for employers (0.6% of the Dutch minimum week-wage). Yet, if the tested intervention is successful and subject to further scaling, it could be considered to a) fully fund the lotteries and b) provide tailored communication for participants without a smartphone in order to minimize inequality in reach and uptake. A fourth limitation is the process of biochemical verification of self-reports. The primary outcome relies on participants willingness to measure and submit their CO-values long after the training has ended. We aim to realize this by offering a time window (c.f., the RS), our retention strategy and by sending reminders. In addition, CO-measurements are an accepted and widely used method [49], but cannot guarantee abstinence over the full 52 weeks. We assess continuous abstinence with two instruments at multiple points in time and include a surprise measurement, but cannot rule out that a negative CO-measurement is the result of only recent smoking cessation.

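### The statement that researchers could not be blinded should not extend to deriving abstinence, which can be done from coded data with arm and organization removed

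*Protocol article*

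**What the plan says.** The Blinding section of the Protocol article states: "Researchers and the management of the companies could not be blinded due to the nature and multi-party coordination of the trial". It does not separate those who recruit and run the lotteries from those who establish who is abstinent.

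On the outcome itself:

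- CO readings are taken at home with an app "that also allows participants to directly share their results with the trial staff via mail" (Smoking abstinence carbon monoxide measurement).
- The same section fixes the handling of gaps and disagreements: "If there is a difference between self-reported abstinence and biochemical validation or when participants do not respond, participants are assumed to have smoked".
- It closes by saying that earlier measurements which conflict with a week-52 claim remove the participant from the continuously abstinent.
- Strengths and limitations concedes that "The primary outcome relies on participants willingness to measure and submit their CO-values long after the training has ended" and gives the remedy: "We aim to realize this by offering a time window (c.f., the RS), our retention strategy and by sending reminders". The window's length is not given in the article.
- Retention gives a single reminder rule: "Participants who do not respond to surveys or other measurements, receive a reminder text message and email".
- The Intervention section provides the coding needed for arm-blind work: "All participants get an anonymized trial-ID at the start of the trial".

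**The concern.** The reason offered for not blinding is the nature of the trial and the coordination between several parties. That is sound for recruiting companies, announcing the lotteries and paying prizes. It does not explain why the person who turns readings and answers into abstinent or not abstinent must know the arm.

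This matters because deriving the primary outcome is not wholly mechanical, and unresolved cases default to smoking. If someone who can see the arm decides whether a late reading counts, or whether an earlier irregularity cancels abstinence, that decision enters the primary comparison directly. At 64 per arm, each participant reclassified in one arm moves that arm's rate by 1/64 = 1.6 percentage points.

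**Working it through.** **1. Does the stated reason reach the outcome?**

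- Under Weeks 14-26, the last lottery is at week 26.
- Strengths and limitations describes six months of follow-up after all lotteries have ended, and says neither arm has a financial reason to cheat at the main outcome point.
- Nothing delivered at week 52 therefore requires knowledge of the arm. At weeks 13 and 26 prize decisions do, but classification for the analysis can be a separate step.
- Randomization already separates the recruiting from the randomizing staff member, so the team can divide roles.

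**2. Where is judgement left?**

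- The CO cut-off (9 ppm or less) and the self-report categories (none, 1–5, more than 5 cigarettes) are fixed.
- The contradiction rule is less so. Before week 52 there are about 13 weekly post-quit tests, one unannounced test and one at week 26: 13 + 1 + 1 = 15 occasions.
- The weekly text asks about any smoking in the past week, whereas continuous abstinence tolerates up to five cigarettes. One weekly yes may or may not be a contradiction.
- Non-response counts as smoking. Read strictly, one missed weekly test would end continuous abstinence. Read leniently, it would not.
- Weekly prizes in the lottery arm depend on these same tests, so missed tests may differ by arm, and the choice of reading could then affect the comparison.

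**3. The plan's own figure.** Inputs from Sample size calculation: 57.5% versus 22.6%, alpha 0.05 (two-sided assumed), power 90%, ICC 0.05, cluster size 8, attrition 15%.

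- Pooled mean p̄ = (0.575 + 0.226)/2 = 0.4005.
- n = [1.96·√(2·0.4005·0.5995) + 1.2816·√(0.575·0.425 + 0.226·0.774)]² / 0.349² = 39.3, rounded up to 40.
- Design effect 1 + 7·0.05 = 1.35; 40·1.35 = 54; 54/0.85 = 63.5, rounded up to 64.

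The stated 40, 54 and 64 reproduce. This point contests no figure.

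**4. How large could arm-dependent classification be?** The article gives no arm-specific response rates, so this rests on assumptions: no true effect, true abstinence p in both arms, and 95% of true abstainers confirmed in the lottery arm but fewer in the control arm.

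- Spurious difference Δ = p·(v_L − v_C), where v is the share of true abstainers confirmed.
- Effective n per arm = 64/1.35 = 47.4.
- With a = p·v_L and b = p·v_C, SE = √{[a(1−a) + b(1−b)]/47.4}, and the two-sided rejection probability is Φ(−1.96 + Δ/SE) + Φ(−1.96 − Δ/SE).
- Example, p = 0.226 and gap 15 points: a = 0.2147, b = 0.1808, SE = 0.0817, Δ/SE = 0.415, rejection about 7.0%.

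| True abstinence | Gap in confirmation | Spurious difference | Participants of 64 | Type I error |
|---|---|---|---|---|
| 22.6% | 5 points | 1.1 points | 0.7 | 5.2% |
| 22.6% | 10 points | 2.3 points | 1.4 | 5.9% |
| 22.6% | 15 points | 3.4 points | 2.2 | 7.0% |
| 57.5% | 5 points | 2.9 points | 1.8 | 5.9% |
| 57.5% | 10 points | 5.8 points | 3.7 | 8.7% |
| 57.5% | 15 points | 8.6 points | 5.5 | 13.5% |

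Staff handling could explain only part of such a gap; participants' own non-response would be the other part. The table shows sensitivity and is not an estimate.

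**5. A check on plausible size.** Suppose the planned 15% attrition means no returned test and is unrelated to abstinence. The true abstainers lost would then be 64·0.226·0.15 = 2.2 in the control arm and 64·0.575·0.15 = 5.5 in the lottery arm.

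**The case against.** The strongest reply is that the article discloses open-label conduct and contradicts itself nowhere: the Blinding, Retention and CO-measurement sections are consistent with one another. That stands.

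A reader might infer that staff who know the arm pursue missing tests harder, or accept late ones more readily, in one arm. The documents do not support this. Retention states one reminder rule without distinction by arm. No section says who sends reminders, whether they are automated, or whether the recipient of a week-52 reading knows the arm; that knowledge is only inferred from the general statement under Blinding. Nor does the article say that staff have discretion over the window. Its length is a detail a condensed article may leave to the full protocol.

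A reader might also take arm-blind handling as the only protection left. It is not. The article has biochemical verification, participants who are not told of the other treatment, a study payment regardless of smoking status, and self-report taken before the CO reading.

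Finally, a fixed cut-off and fixed answer categories leave little to judge, and blinding staff cannot correct unequal response by participants. Both are fair. The first does not cover the contradiction rule, where the weekly question and the five-cigarette allowance leave room for interpretation.

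**Conclusion.** The point holds as a modest improvement to the design, not as an error or a demonstrated bias. The exclusion of blinding is wider than its stated reason: it should cover recruitment and delivery, and need not cover derivation of abstinence.

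The size of any bias is unknown. On the assumptions in the table it runs from 1.1 to 8.6 points, with type I error of 5.2% to 13.5%. That is small against the planned 35 points, though not negligible against the 15 points that the Background cites from an earlier workplace incentive trial.

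A reader might picture three to five results altered by staff in one arm, which would be 3/64 = 4.7 to 5/64 = 7.8 points. The documents give no basis for that count. It exceeds the 2.2 abstainers expected to be missing in the control arm, and would be 54% to 91% of the 5.5 in the lottery arm (3/5.52 and 5/5.52).

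**What to change.** - In Blinding, limit the statement to recruitment and intervention delivery.
- Derive abstinence at weeks 13, 26 and 52 by script, or by existing staff, from a file keyed by trial-ID with arm and organization removed. Organization must go too, because whole organizations are allocated and so it reveals the arm.
- Write down one acceptance window and one contradiction rule, covering a weekly yes and a missed weekly test, and apply both identically in the two arms.
- Lock the classification, then merge allocation and organization for the multilevel model.
- Keep the uniform reminder rule in Retention.

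The cost is small but not nil: one extra data-handling step with IDs and staff that already exist. Because it works on stored data, it can cover participants already followed up as well as those continuing into 2023, without changing follow-up midway. It does not remove unequal response by participants themselves.
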